## Abstract

**Background:**

Academic mentoring plays a critical role in monitoring student progress, maintaining academic integrity, identifying early signs of risk, and delivering personalized guidance to improve learning outcomes. Traditionally, this has relied on face-to-face interactions; however, advancements in artificial intelligence (AI) have introduced new opportunities for AI-assisted mentoring. While promising, many existing AI models for student monitoring and risk identification are complex and difficult to implement in real-world academic settings. To address this challenge, the present study validates a simplified AI comentor model designed to efficiently identify at-risk students and support continuous academic monitoring focused on pedagogy.

**Methods:**

This study employed a prospective mixed-methods pilot design to evaluate the feasibility, acceptability, and analytic agreement of an AI-assisted assessment framework in medical education. Participants included approximately 40 undergraduate medical students and faculty assessors. Primary outcomes focused on implementation feasibility and acceptability, assessed using structured student and faculty surveys, system-usage metrics, and qualitative feedback. Secondary outcomes evaluated the analytic agreement between AI-derived competency profiles and faculty assessments. The AI component used unsupervised machine learning–based clustering to group students according to multidimensional performance indicators, without prior labels. Agreement was examined using confusion matrices, percentage agreement, and Cohen's Kappa, reported with confidence intervals to account for the exploratory sample size. Given the pilot nature of the study, resampling-based validation (repeated stratified k-fold cross-validation) was used to assess stability rather than definitive diagnostic accuracy. Ethical approval was obtained, and all data were deidentified before analysis.

**Discussion:**

This study will be conducted on a cohort of 40 students from a reputed Health Sciences College, UAE, to evaluate the integrity of a proposed AI comentoring model for monitoring academic performance throughout a semester. The AI models (supervised and segmentation engines) will be tested at two time points: the 5th and 10th weeks. At each time point, categorized student performance data will be uploaded to the AI platform, based on pedagogical parameters, and used to generate a personalized text draft automatically (local pseudonymization + institutional mail merge workflow). To assess the integrity of the used AI, the investigator will perform a manual evaluation of each student's risk status at both checkpoints, alongside statistical analyses. If successful, the system may alleviate the workload of human mentors, enable timely interventions for at-risk students, and enhance overall student performance and retention.

## Introduction

Monitoring the academic progress of students is widely recognized as a valuable form of personalized support, allowing mentees to gain insights from the expertise of their mentors to enhance their learning and achieve their personal goals. However, the growing need to incorporate artificial intelligence (AI) into mentoring within higher education raises critical considerations such as ensuring data integrity, safeguarding system security, maintaining confidentiality, preventing bias, fostering trust, and promoting transparency in algorithms (1).

AI-supported mentoring represents a digitally advanced and scalable approach that replicates the role of mentors by automating tasks such as delivering personalized feedback, providing tailored recommendations, and guiding individual learning paths to improve performance in the academic careers of students (1).

In general, both the face-to-face approach and the AI-supported mentoring approach have their own advantages, disadvantages, and ethical challenges. AI cannot feel or interact with empathy and compassion, which highlights the continued necessity for human teachers and mentors (2). While human mentors can offer personalized support to only a limited number of students, AI-supported mentoring has the potential to broaden access and minimize favoritism.

The unprecedented capabilities of AI risk engines—such as generating human-like text and enabling automated conversations (message generation layer)—carry significant implications across various sectors, including education and healthcare (3), based on each student's unique abilities, interests, and needs, thereby enhancing the learning process (4–13).

The integration of AI into mentorship programs may assist teachers by reducing their workload, allowing them to focus more on creating innovative lesson plans and engaging in professional development. Although data feeding into AI must adhere to key ethical principles, such tasks are vital for real-time monitoring of a large volume of student cohorts, addressing the demands and opportunities of the future (1, 3).

Previous risk prediction models developed by researchers relied on statistical analyses and calculations that were often too complex for faculty to easily understand and apply. Hence, the current study proposes to validate both supervised and unsupervised AI mentoring, using ChatGPT-4 and a predictive risk engine (rules + ML models) to recognize students at risk and provide them mentoring advice to help achieve their learning goals.

The AI Risk Identification Assistance System (AIAS) is conceptualized as a learning analytics early-warning system integrated with mentoring practice. The risk engine identifies students who may not meet the course benchmark (e.g., <65% continuous assessment), while the mentoring layer delivers self-regulated learning (SRL)-oriented prompts and facilitates timely human follow-up at weeks 5 and 10.

The novelty and originality of this project lie in its simplicity and practical application. Earlier studies utilized complex calculations and did not deeply explore how different AI applications align with specific pedagogical models or teaching strategies across disciplines and contexts. They focused on formulas to identify at-risk students and offered automated academic advice through AI. Furthermore, these studies often lacked regular follow-up phases to track student progress and did not test AI-driven mentoring models (14, 15).

Our proposed AI mentoring model is expected not only to recognize at-risk students based on their pedagogical assessment system but also to provide personalized advice to ensure their academic success. This will be achieved through regular automated reminders, risk reports, and academic advice generated by supervised and segmentation engines (unsupervised AI models). The role of the faculty is to simply upload the necessary data to the chatbot. The study will be conducted on students from Health Science at the College of Health Sciences, Gulf Medical University (GMU), UAE, for a semester.

## Materials and methods

### Study design

This study employs a prospective mixed-methods pilot design to evaluate the implementation and exploratory analytic performance of an AI-assisted assessment framework in undergraduate medical education. In line with its pilot intent, the study is designed to separate implementation feasibility and acceptability (primary outcomes) from analytic agreement between AI-derived outputs and faculty assessments (secondary outcomes). The study does not aim to establish diagnostic accuracy or predictive validity but rather to generate preliminary evidence to inform subsequent confirmatory research.

### Study setting and participants

The study was conducted in an undergraduate medical education program at a single academic institution. Approximately 40 medical students enrolled in the target course, and faculty assessors involved in student evaluation were invited to participate. All participants provided informed consent before data collection. Students were assessed as part of routine educational activities. Faculty assessors had prior experience with structured assessment rubrics and received standardized orientation to the study procedures to minimize variability in scoring.

### AI-assisted assessment framework

The AI component consisted of an unsupervised machine learning–based clustering module designed to group students according to multidimensional performance indicators derived from assessment artifacts (e.g., rubric scores, task completion metrics, and structured feedback variables). No outcome labels or performance categories were predefined, and the algorithm did not generate pass/fail or diagnostic classifications. Clustering outputs were interpreted as exploratory competency profiles intended to support sensemaking and reflection, rather than automated judgment. The AI system functioned strictly as a decision-support tool, with all summative decisions retained by faculty.

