#### Secondary outcomes: analytic agreement

Secondary outcomes focused on exploratory agreement between AI-derived competency clusters and faculty assessment outcomes. Agreement was examined using the following:
Confusion matrices comparing AI cluster membership with faculty-assigned performance categories;Percentage agreement; andCohen's Kappa, reported with 95% confidence intervals.These analyses were conducted to explore alignment patterns rather than to claim validation or diagnostic performance.

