### Data processing

This pilot feasibility study focuses on a single group of students from the Bachelor Program at College of Health Sciences (CoHS), GMU, with a minimum sample size of 40 participants to assess the feasibility and acceptability of the approach. Given the pilot sample size (*n*=40), model evaluation will use repeated stratified k-fold cross-validation (or leave-one-out CV) and bootstrap confidence intervals to reduce instability from fixed splits. A pre–post analysis will be conducted to evaluate the significance of differences in the occurrence of high-risk students at each stage of data collection (across three time points). The third assessment point will be their final score and passing percentage. Subsequently, this study may be expanded to a larger sample size using a cluster-randomized group study design. The project will utilize Python and related libraries.

Additional automated alerts and academic advice generated by AI will be thoroughly cross-verified by the investigators with respect to the target students and mentors. In parallel, the investigators will manually analyze student performance using data from the three designated time points [human-in-the-loop governance (mentor approval and escalation)]. This process will allow the investigators to confirm the integrity, accuracy, and functionality of the newly proposed AI mentorship model. A survey will also be conducted among the targeted students and faculty to assess their responses, success rates, and the accuracy of the proposed AI co-mentoring model in tracking academic progress. The present study is designed to use quantitative data, while qualitative data from the survey will be used for validation purposes. Figure 1 provides an overview of the intended workflow in the form of a flowchart.

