#### Interpretation framework

Analytic results were interpreted within a decision-support paradigm, recognizing faculty assessment as the reference standard and AI outputs as supplementary insights. Statistical findings were used to characterize alignment patterns rather than to adjudicate correctness or automate evaluative decisions.

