## Discussion

This study proposes and validates a simplified, integrated AI-assisted comentoring model that combines both supervised and unsupervised machine learning techniques to identify at-risk students and enhance academic performance among Health Sciences students at the CoHS, GMU. By comparing supervised models reliant on labeled datasets and evaluating them using established metrics such as accuracy and precision with a segmentation engine that detects hidden patterns and student groupings, the study aims to determine evaluation feasibility and validity, including agreement with human mentor ratings.

Previous research in academic risk engines utilized algorithms such as k-Nearest Neighbors, decision trees, artificial neural networks, and Naive Bayes classifiers to generate early-stage predictions of academic performance (16). These models often relied on preprocessed datasets and were applied repeatedly throughout the semester to refine predictions and deliver personalized feedback to students. Building upon this, the current model integrates natural language processing capabilities to process large volumes of student data, identify academic risks at an individual level, and generate student-specific messages (17).

The use of AI-powered chatbots such as ChatGPT enhances this model's engagement capacity—particularly in the context of public health and higher education—by offering responsive and context-aware support that adapts to diverse learning needs (18). Furthermore, the comentoring approach automates core mentoring tasks such as tracking attendance, monitoring CGPA progression, and analyzing assignment completion patterns, allowing for more timely and targeted interventions (Table 5). These automated updates and alerts not only inform students of their academic standing but also reduce dependency on remedial coursework by promoting early corrective action.

**Table 5 T5:** Risk mapping.

Mapping variable	Construct	Measure/indicator	Rationale
Assignment submission	Academic self-management	On-time vs delayed submissions	Indicator of organization and time management
Written exam scores	Theoretical knowledge	Percentage score in core physiotherapy modules	Reflects understanding of foundational concepts
Practical skills assessment (OSCE)	Clinical competence	Objective Structured Clinical Examination score	Assesses applied clinical skills

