Feasibility challenges such as data quality, technical limitations, and the risk of systemic errors will be mitigated through model fine-tuning and human oversight via face-to-face mentoring where needed. Participants will be informed of potential errors issues with AI mentoring, if any, in advance to prevent confusion or panic. A glossary of key terms is appended in Table 7.

**Table 7 T7:** Glossary of key terms.

Term	Definition
AIAS (AI Risk Identification Assistance System)	The AIAS refers to a system in which artificial intelligence tools are used to support and enhance human decision-making or analysis, with final judgment and control remaining with the human user.
Supervised model	A predictive model trained on historical student data with known outcomes, used to classify future student risk.
Unsupervised model	A model that identifies patterns or clusters in student data without prelabeled outcomes, used to detect groups of students with similar risk profiles.
Risk report	A structured summary of a student's likelihood of academic difficulty, including risk labels and recommended support actions.
Human validation	The process by which trained evaluators independently review and confirm risk status, ensuring AI-generated outputs align with expert judgment.

In conclusion, this pilot feasibility study not only explores the comparative strengths of supervised and segmentation engines in risk prediction, but also contributes to the ongoing development of effective validated AI-assisted mentoring systems focused on pedagogy and academic performance outcomes. The study findings are expected to provide critical insights into the practicality, reliability, and impact of integrating AI into student support services and lay the groundwork for future large-scale implementations across educational institutions. Each assessment component has been already mapped to the course learning outcomes.

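### The clustering inputs and the faculty reference appear to share faculty scores, so kappa probably overstates independent agreement and cannot alone support accuracy or validity

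*Protocol article*

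**What the plan says.** The AI-assisted assessment framework section describes an unsupervised clustering of students on performance indicators "derived from assessment artifacts (e.g., rubric scores, task completion metrics, and structured feedback variables". This is a list of examples, without weights.

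Study setting and participants describes the people who score: "Faculty assessors had prior experience with structured assessment rubrics and received standardized orientation to the study procedures to minimize variability in scoring". No other rubric scorer is mentioned.

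The secondary outcome is agreement, using percentage agreement, Cohen's kappa with 95% confidence intervals, and "Confusion matrices comparing AI cluster membership with faculty-assigned performance categories". The Interpretation framework commits to "recognizing faculty assessment as the reference standard and AI outputs as supplementary insights".

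Alongside this, Data processing says that "the investigators will manually analyze student performance using data from the three designated time points". The glossary (Table 7) describes human validation as a process in which "trained evaluators independently review and confirm risk status, ensuring AI-generated outputs align with expert judgment".

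Two statements of purpose pull apart. The secondary-outcome section says the analyses are done "to explore alignment patterns rather than to claim validation or diagnostic performance". The Discussion says "the study aims to determine evaluation feasibility and validity, including agreement with human mentor ratings", and Data processing expects the manual analysis to confirm that the model is accurate.

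**The concern.** Kappa corrects for chance agreement. It does not correct for agreement that arises because both classifications draw on the same measurements. If a rubric mark is too high for a student, it can raise the student's cluster and the student's faculty category together, and the two then agree on an error. This is incorporation bias.

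The planned analysis has nothing that separates two explanations of a moderate kappa: the AI recognises students at risk, or the AI re-sorts marks that faculty have already given. The planned safeguards do not help. Confidence intervals express sampling error only, and repeated cross-validation carries the same overlap into every fold. Because the results are meant to inform larger confirmatory studies, a kappa that cannot be interpreted would be carried forward.

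**Working it through.** **Step 1: how far the text establishes overlap.**

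| Link | Status in the article |
|---|---|
| Rubric scores and structured feedback enter the clustering | Stated, as examples (AI-assisted assessment framework) |
| Faculty produce those scores | Strong inference (Study setting and participants) |
| Faculty categories are the comparator and reference | Stated (Secondary outcomes; Analysis of secondary outcomes; Interpretation framework) |
| Categories rest on the same marks or come from the same assessors | Not stated |
| Categories rest on separate data | Not stated; the glossary says only that evaluators review independently |

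The investigators' manual check also uses the students' performance data from the study time points. The article's only numerical course-performance categories, in Table 2, are cuts on a mark total (20 + 20 + 25 = 65). Table 2 is labelled as the AI model's metrics, so it does not prove that faculty use the same cuts.

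**Step 2: size.** The article gives no expected kappa, mark reliability, cluster count or category count, so there is no figure to reproduce. Only n = 40 comes from the document; every other value below is an assumption. Kappa is (po − pe)/(1 − pe), where po is observed agreement and pe is chance agreement. Clusters were matched to categories by the rank of the cluster mean.

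*Model A, full overlap.* Three mark components; k-means with three clusters; faculty category cut at the 25th and 60th percentiles of the mean of the same marks; 600 replicates. The comparison clusters an independent set of marks of equal reliability.

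| Reliability | Shared marks | Independent marks | Difference |
|---|---|---|---|
| 0 | 0.35 | 0.00 | 0.35 |
| 0.3 | 0.53 | 0.22 | 0.31 |
| 0.5 | 0.63 | 0.35 | 0.28 |
| 0.7 | 0.67 | 0.50 | 0.17 |

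Two further runs of this model agreed with these means within 0.02.

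*Model A, one of three components shared* (400 replicates).

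| Reliability | One shared | Independent | Difference |
|---|---|---|---|
| 0 | 0.09 | 0.01 | 0.08 |
| 0.3 | 0.29 | 0.21 | 0.08 |
| 0.5 | 0.42 | 0.35 | 0.07 |
| 0.7 | 0.55 | 0.49 | 0.06 |

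Another run gave 0.06 to 0.09.

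*Model B, a different structure.* One latent competence; clustering on rubric, task completion and feedback; faculty category as tertiles of the rubric score, against tertiles of an independent rating of equal reliability; 600 replicates.

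| Reliability | Same rubric score | Independent rating | Difference |
|---|---|---|---|
| 0.5 | 0.41 | 0.26 | 0.15 |
| 0.7 | 0.50 | 0.37 | 0.13 |
| 0.85 | 0.57 | 0.49 | 0.08 |

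The mean shift was upward in every setting tried.

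**Step 3: sampling error for scale.** With n = 40 and three balanced categories, pe = 1/3, and the approximate 95% half-width is 1.96 × √[po(1 − po)/(40(1 − pe)²)]. For kappa 0.4, po = 0.4 × 2/3 + 1/3 = 0.60 and the half-width is 0.23. For kappa 0.6 it is 0.21, and for kappa 0.8 it is 0.16.

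**The case against.** A reader might infer that kappa is inflated by construction, by 0.17 to 0.35. The documents do not support that. Nothing says that the categories are computed from the clustered marks or assigned by the assessors who gave them. The inputs are an example list that includes task completion. The 0.17 to 0.35 range belongs to the full-overlap model, and its top end also needs marks with no true signal. The partial-overlap shifts are smaller than the confidence-interval half-width at 40 students. All of this stands.

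Shared inputs can also be intended. Whether automated sorting reproduces human sorting of the same record is a fair question for a tool meant to save mentor time. Agreement is a secondary, exploratory outcome here, with cautious interpretation promised. This lowers the severity. It does not remove the point, because Data processing and the Discussion go beyond that question to accuracy and validity. A bias smaller than the interval half-width is still a bias, and the interval does not show it.

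How faculty assign categories may well be set out in the full protocol, so its absence from an article is not the complaint. The complaint is that the stated inputs and the stated reference appear to overlap and the planned analysis has no comparison that reveals it.

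**Conclusion.** The point holds in a limited form. The text supports an apparent overlap between the clustering inputs and the faculty reference, and the likely direction of bias in kappa is upward. Kappa therefore cannot, by itself, show independent agreement, accuracy or validity.

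The amount cannot be computed from the article. Under the assumed models it is about 0.06 to 0.15 kappa units with partial overlap, rising to about 0.35 only in the extreme case of identical marks without true signal. These figures rest on the assumed reliabilities, three clusters and chosen cuts.

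It would also be tempting to call the main kappa an upper bound. That is not justified: an estimate from 40 students is not a bound, and with one shared component the independent kappa equalled or exceeded the shared one in 30 to 40% of replicates. This is a worthwhile improvement to a secondary analysis and leaves the primary feasibility outcomes untouched.

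**What to change.** Keep the planned kappa and add two items to Analysis of secondary outcomes.

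1. **Sensitivity kappa.** Repeat the clustering without the faculty-scored rubric and feedback variables, using features the article already names: task completion, submission timeliness and attendance. Report this kappa with its 95% confidence interval beside the main one. State that a fall mixes removed overlap with lost information. Faculty may also take attendance and submission into account, so full independence is not assured.
2. **Total-mark comparator.** Report the kappa of a simple total-mark rule against the same faculty categories. This is descriptive and not a hurdle for the AI to beat: if faculty cut the same total at the same points, the rule has kappa 1.00 and no clustering could exceed it. If the rule agrees with faculty about as well as the clusters do, the clustering has shown no added agreement.

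In the Interpretation framework, state that the main kappa reflects agreement on partly shared marks and likely overestimates independent agreement, without calling it an upper bound. A sentence on who assigns the categories, and from which data, would let readers judge the overlap.

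The cost is two extra runs of an existing script and a few lines of text, with no new data. The reduced-feature clustering will be noisier, and the headline agreement may look less favourable.

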### A sample risk assessment summary by a supervised AI system

A sample CHATGPT-4 automated risk report with a message generation layer [templated or large language model (LLM)-assisted drafting; student-specific academic counseling messages] is provided in the following (Supervised AI mentoring model):

Sample Automated Risk Report by AI (Based on Analysis of Academic Performance)

Dear Student,

Subject: Academic Progress/Student at Risk/Academic Counseling

Based on the latest academic performance evaluation for the course [Course Name – Course Code], you have been identified as at risk of not meeting the passing criteria, as your current performance falls below the required benchmark.

Your academic progress as of [Date] is summarized as follows:

Attendance: 80%

Class Test: 55%

Coursework: 65%

Midsemester Exam: 65%

Total Average Score: 61.67%

[Passing benchmark: You must achieve a minimum score of 65%.]

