### Statistical analysis

Statistical analyses were conducted in alignment with the pilot and exploratory objectives of the study, with clear separation between primary implementation outcomes and secondary analytic agreement outcomes. No analyses were intended to establish diagnostic accuracy or predictive validity.

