#### Analysis of secondary outcomes

Secondary analyses focused on exploratory agreement between AI-derived student clusters and faculty assessments. AI outputs were treated as unsupervised groupings, without prespecified performance labels. Agreement between AI cluster membership and faculty-assigned performance categories was examined using (1) confusion matrices, (2) percentage agreement, and (3) Cohen's Kappa, with 95% confidence intervals

Given the limited sample size, Kappa values were interpreted cautiously, emphasizing direction and magnitude rather than threshold-based validity claims.

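### The agreement statistics are defined only for unlabelled clusters and not for the risk engine whose labels prompt student messages, although the article promises that this engine is tested, checked for accuracy and compared

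*Protocol article*

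**What the plan says.** **What is analysed.** The section on the AI-assisted assessment framework states: "The AI component consisted of an unsupervised machine learning–based clustering module designed to group students". It adds: "No outcome labels or performance categories were predefined, and the algorithm did not generate pass/fail or diagnostic classifications". Analysis of secondary outcomes follows this: "Secondary analyses focused on exploratory agreement between AI-derived student clusters and faculty assessments". Resampling and stability assessment applies cross-validation to the alignment of clusters with assessments. The opening of Statistical analysis states: "No analyses were intended to establish diagnostic accuracy or predictive validity". Study design says the same of the study's aims, and the secondary outcome section disclaims validation.

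**What is deployed.** The Introduction describes a risk engine of rules plus machine-learning models that picks out students likely to miss a course benchmark, for example below 65%. The sample supervised report tells the student "you have been identified as at risk of not meeting the passing criteria". Tables 2 to 4 set score thresholds with named risk categories, reported at weeks 5 and 10. Data privacy says that the system outputs risk labels.

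**What is promised.** The Abstract says that both engines will be tested at weeks 5 and 10. Data processing says that manual analysis will confirm the model's accuracy, and plans a survey "to assess their responses, success rates, and the accuracy of the proposed AI co-mentoring model". The Discussion speaks of comparing supervised models and "evaluating them using established metrics such as accuracy and precision with a segmentation engine that detects hidden patterns", and closes by saying that the study "explores the comparative strengths of supervised and segmentation engines in risk prediction".

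**The concern.** The article describes two AI components. One groups students without labels. The other assigns a risk category that leads to a drafted message and, under Table 6, to escalation. The statistical plan attaches its agreement measures to the first, while the article's claims mostly concern the second.

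A reader who sees a kappa in the final report, next to text about identifying at-risk students, would take it as the agreement of the risk labels with faculty judgement. It would be nothing of the kind. The secondary outcome would then not measure what the article says it sets out to examine, and the promised comparison of engines would have no defined statistic behind it.

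**Working it through.** No sample-size or accuracy figure is at issue, so the check sets the sections side by side.

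**1. Which component has which statistic?**

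| Item in the article | Clusters | Rule/supervised risk engine |
|---|---|---|
| Confusion matrix against faculty (secondary outcomes) | yes | not stated |
| Percentage agreement | yes | not stated |
| Cohen's kappa with 95% CI | yes | not stated |
| Resampling (Resampling and stability assessment) | yes | not stated |
| Predefined risk categories (Tables 2–4) | denied in Methods | yes |
| Accuracy and precision (Discussion) | no | promised |
| Comparison of the two engines (Discussion) | promised | promised |

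All four named procedures belong to the clusters and none to the engine that flags students.

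**2. Does other text fill the gap?** Four plans outside the Statistical analysis section could do so.
- Cross-validation with bootstrap intervals (Data processing): neither the model nor the metric is named. Where cross-validation reappears under Statistical analysis, it is tied to clusters.
- Pre–post analysis of how often high-risk status occurs (Data processing): it uses risk labels, but it measures change over time, not agreement with a human rating.
- Manual cross-verification of alerts and parallel manual analysis (Data processing): said to confirm accuracy, with no statistic.
- Manual rating of each student's risk status at both checkpoints (Abstract): accompanied by unspecified statistical analyses.

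None pairs the risk engine with an agreement or accuracy metric, and none carries risk labels into the secondary analysis.

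**3. Is the description of the clustering module consistent?** No. Methods say it has no predefined categories. Table 1, headed as output of an unsupervised system, gives High and Medium risk levels for each area.

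**4. Could the engine's category be cross-tabulated today?** Table 2 classifies the summative score out of 65 as above 80% (>52), between 70% and 80% (>45.5), or below 60% (<39). Scores from 39 to 45.5, a span of 45.5 − 39 = 6.5 points, have no category. The 65% benchmark lies inside that gap: 0.65 × 65 = 42.25.

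The article's sample student has a class test of 55%, coursework of 65% and a midsemester exam of 65%.
- Unweighted mean, the article's own figure: (55 + 65 + 65)/3 = 61.67%.
- With the Table 2 weights: 0.55 × 20 + 0.65 × 20 + 0.65 × 25 = 11 + 13 + 16.25 = 40.25, and 40.25/65 = 61.92%.

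By either calculation the student is below 65% and is flagged in the sample report, but has no summative category in Table 2. An ordered agreement analysis therefore cannot be run until the categories are reconciled.

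**The case against.** The best defence is that this is a pilot whose primary outcomes are feasibility and acceptability of the whole AI-assisted process, that accuracy and validation are disclaimed several times, and that a mentor approves each message before it is sent. A condensed article may also leave detail to a full protocol or analysis plan. Much of this stands. The primary outcomes are intact, and human review limits what a wrong label can do. It does not remove the conflict, because the article positively fixes the agreement analysis on unlabelled groupings and, in other sections, promises something else. That is contradictory content, not omitted detail.

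Some stronger readings are tempting but not supported:
- *The risk engine is never analysed.* Data processing plans cross-validation, a pre–post analysis and manual verification. The fault is that none names this engine together with a metric.
- *Accuracy is judged only by an opinion survey.* Manual verification is planned alongside the survey.
- *The article concludes on accuracy.* It reports no results, only aims and expectations.
- *The supervised model has no training data.* The glossary in Table 7 speaks of historical data with known outcomes, and the Discussion of labelled datasets. Their source is a detail that an article may leave out.
- *The precision of sensitivity at 40 students can be quantified.* The documents give no proportion of high-risk students, and any such figure would rest on an outside assumption.

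**Conclusion.** The concern holds as an inconsistency between the planned secondary analysis and the component and claims it is meant to serve. All of the named agreement and resampling procedures apply to unlabelled clusters; none is defined for the engine whose labels prompt student messages. The promises of testing, accuracy and comparison cannot stand beside the disclaimers of accuracy, predictive validity and validation. Methods and Table 1 also disagree on whether the unsupervised system issues risk levels.

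The effect is confined to an exploratory secondary outcome and to the claims built on it. It should be corrected before analysis, but it does not undermine the primary outcomes. The conclusion rests on the article's text alone; a full analysis plan that defines a statistic for the risk engine would close the analytic gap, but not the conflict of wording within the article.

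**What to change.** 1. Add one exploratory secondary analysis: a cross-table of the risk engine's category against the investigator or faculty manual risk status, separately at weeks 5 and 10, with cell counts, percentage agreement and weighted kappa with 95% confidence intervals. Keep the clusters as descriptive output.
2. First reconcile Table 2 so that every score has a category, and say which table supplies the engine's category, since Tables 2, 3, 4 and 6 use different scales. Where the boundaries lie is for the study team to decide.
3. State that the manual rating is made without sight of the AI label. The glossary calls human review independent but does not say this. State also that kappa is partly circular if raters use the same scores as the rule.
4. Correct the AI framework section to cover the label-issuing engine, and reconcile it with Table 1.
5. In the Abstract, Introduction, Data processing and Discussion, replace the language of validation, accuracy and precision, and comparative strengths with exploratory agreement. Call the survey item perceived accuracy.

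**Cost:** wording changes, one extra table and the work of completing the categories. The manual ratings are already planned at both checkpoints. The price is weaker claims, which match what the article's own disclaimers allow.
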